#### Bone Movements

The differences between the residual bone movement with the EV and the traditional suction suspension will be determined in 6 DOF for each participant. Briefly, group differences for tibial rotations and translations as well as total excursions of the bone for each suspension condition will be compared during the gait cycle. Paired *t* tests will be performed and a between-participant factor at 2 levels (EV on and EV off) will be used. A hierarchical linear model will be used to evaluate the tibial range of motion (ie, maximum translation and rotation) as a function of tibial position and potential confounding factors (eg, gender, age, etiology, and time since limb loss). The hierarchical linear model will also be used to evaluate the tibial motion path and the effect of rate during the 3 different activities.

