### Prosthetic Suspensions

Individuals with transtibial limb loss will be provided with a prosthesis capable of being suspended via both EV and traditional suction, with the prosthetic ankle-foot devices they currently use. Participants will be tested under 2 conditions: with the EV suspension active and with the EV inactive (traditional suction suspension). The order of the conditions will be counterbalanced.

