### DSX Experimental Design

Following the 4-week acclimation period, the participants will be evaluated at the Rutgers New Jersey Medical School DSX facility. To evaluate the 6 DOF kinematics of the residual limb within the socket, participants will separately walk on a treadmill at a self-selected speed, at a speed 10% faster, and during a step-down task from an 18 cm–high platform. The DSX system will be oriented such that all tasks can be recorded with the same configuration. These movement tasks will be completed under 2 conditions: with the EV suspension active and with the EV system inactive (traditional suction). For testing with the traditional suction suspension (EV inactive), the vacuum connector will be replaced with a PushValve (Ottobock, Inc) [11]. A randomized block, crossover design will be used to evaluate the residual limb-socket fit. A group of 11 participants (group 1) and a group of 10 participants (group 2) will be formed. Participants in group 1 will first be tested in the DSX system with the EV on, and then, they will repeat all procedures with the EV inactive. Participants in group 2 will first be tested in the DSX system with the EV inactive, and then, they will repeat the tasks with the EV active. After each suspension method is applied, participants will be instructed to perform normal daily activities for 2 hours to allow for acclimation and for transient changes (eg, volume loss) to manifest. A period of 2 hours was chosen so that both conditions can be tested on the same day while still capturing 90% of the volume loss during socket use [1]. Up to 4 trials of DSX will be conducted for each task for each socket condition, giving a maximum of 24 trials per participant. For each task, DSX data will be collected and analyzed to determine the underlying bone movement and skin strain with respect to the socket. Separate CT scans of the residual limb and socket will also be captured for each participant to generate participant-specific socket and bone models of the residual limb for tracking kinematics.

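### The elevated vacuum versus suction comparison is a same-day, two-order crossover, but it is tested with paired t tests that ignore order, which costs power if limb state drifts during the day

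*Protocol article*

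**What the plan says.** DSX Experimental Design fixes the design: "A randomized block, crossover design will be used to evaluate the residual limb-socket fit". It continues: "A group of 11 participants (group 1) and a group of 10 participants (group 2) will be formed". Group 1 is tested with EV on and then off, group 2 the other way round. Prosthetic Suspensions adds: "The order of the conditions will be counterbalanced".

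Each condition follows 2 hours of daily activity, "to allow for acclimation and for transient changes (eg, volume loss) to manifest". That interval was chosen so that "both conditions can be tested on the same day while still capturing 90% of the volume loss during socket use".

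The suspension contrast is set out in Bone Movements: "Paired *t* tests will be performed and a between-participant factor at 2 levels (EV on and EV off) will be used". Skin and Liner Deformation refers back to the same tests. Neither section gives the comparison a period or order term.

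Bone Movements also describes a second analysis: "A hierarchical linear model will be used to evaluate the tibial range of motion (ie, maximum translation and rotation) as a function of tibial position". The model is also to carry possible confounders, and the examples given are all participant characteristics. The same model is to address motion path and the effect of rate across the three activities. Suspension and period are not named in it.

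**The concern.** The design randomises and counterbalances order, and the analysis then discards it. Both conditions fall on one day, so the second is measured after about 2 more hours of wear than the first, in a trial that expects limb volume to change with wear. A shift between the two sessions would raise the EV-minus-suction difference in one order group and lower it in the other. The paired t test treats that systematic split as random scatter.

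At stake is precision. The sample size of 21 rests on effect sizes of 0.77 and 0.75, where the reserve over 90% power is 2 percentage points or less. The text also calls EV on/off a between-participant factor although every participant receives both conditions, so the structure of the comparison is misdescribed where it is specified.

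**Working it through.** **Inputs.** From Power Analysis: paired t test, α = 0.05 (two-sided assumed, as sidedness is not stated), N = 21, effect sizes 0.77 (femur pilot, 0.5 cm difference), 0.75 (skin shear strain) and 1.75 (tibial translation). From DSX Experimental Design: order groups of 11 and 10. The documents give no period effect, so its size below is an assumption.

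**Step 1: the plan's own figures.** The exact noncentral t with n − 1 df needs, for 90% power:
- effect size 0.77: n = 20 (stated 21; power at 21 is 91.8%)
- effect size 0.75: n = 21 (power 90.5%)
- effect size 1.75: n = 6 (power 92.3%; above 99% at 21)

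The stated sizes are sound on their own inputs.

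**Step 2: where a period effect goes.** Let τ be the EV-minus-suction effect and π the shift from first to second session, both in SDs of the paired difference. The expected difference is τ − π in the EV-first group and τ + π in the suction-first group.

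- Mean over all 21: [11(τ − π) + 10(τ + π)]/21 = τ − π/21. The bias is 4.8% of the period effect.
- Expected sample variance: 1 + π²(21 − 1/21)/20 = 1 + 1.048π². This is 1.26 at π = 0.5 and 2.05 at π = 1.

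On the protocol's scale, the implied SD of differences is 0.5/0.77 = 0.65 cm, so 0.25, 0.5 and 1 SD are 0.16, 0.32 and 0.65 cm.

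**Step 3: power with and without the period term.** For the paired t test, the mean is normal with variance 1/21, and 20 times the sample variance is noncentral chi-square (20 df, noncentrality 20.95π²). Integrating over the latter gives exact power. The adjusted analysis averages the two groups' mean differences. Its variance is (1/11 + 1/10)/4 = 0.0477, against 1/21 = 0.0476 unadjusted, on 19 df. Ranges show the two directions of the period effect.

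| Assumed period effect | Paired t, 0.77 | Paired t, 0.75 | Type I error, paired t |
|---|---|---|---|
| 0 | 91.8% | 90.5% | 5.0% |
| 0.25 SD | 89.9 to 91.6% | 88.3 to 90.2% | 4.4% |
| 0.5 SD | 85.1 to 89.3% | 83.0 to 87.6% | 3.0% |
| 0.75 SD | 76.2 to 84.6% | 73.5 to 82.5% | 1.6% |
| 1 SD | 62.9 to 76.8% | 59.6 to 74.1% | 0.7% |
| Period-adjusted, any size | 91.6% | 90.2% | 5.0% |

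Simulation with 100,000 replicates per scenario agrees. With no period effect, adjustment costs 0.2 to 0.3 percentage points. At effect size 1.75 the paired test keeps essentially 100% power up to a 1.5 SD period effect.

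**The case against.** The period effect is assumed, and the text points towards a modest one. If 2 hours captures 90% of volume loss, most of it has occurred before the first test and about 10% remains. That stands: the 0.5 and 1 SD rows are large against a 0.5 cm target, and at 0.25 SD power stays close to 90% or above.

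Direction matters too. Validation of DSX Strain Measurements cites 1.3 cm displacement for vacuum and 1.8 cm for suction. If later wear increases motion, the larger, EV-first group shows the larger EV benefit, and the upper end of each range applies. The lower ends alone would overstate the loss.

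Three stronger readings are tempting, and the documents do not support them:

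- A reader might infer that ignoring order materially biases the EV estimate or produces false positives. The 11/10 counterbalance limits the bias to period effect/21, and the unadjusted test is conservative.
- A reader might infer that the hierarchical model adjusts away part of the EV effect by conditioning on tibial position. The article assigns the EV contrast to the paired t tests, leaves tibial position undefined and gives an open-ended confounder list. The point is a caution should that model be used for EV.
- A reader might take the EV estimate by order group as a check on carryover. The two groups' difference carries the period effect (2π in the notation above). Differential carryover moves both groups' average by half its size, and neither that comparison nor a period term removes it.

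It may also be said that an article leaves model terms to the analysis plan. That does not answer the point, because the article names the test for the suspension contrast, and that test has no place for order.

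**Conclusion.** The point holds as an avoidable loss of precision, conditional on a period effect whose size is unknown. Power falls below the planned 90% in both directions from 0.5 SD upward at effect sizes 0.77 and 0.75. At 0.25 SD the loss is about 2 points or less, and at 1.75 there is none of consequence. The estimate itself is barely affected. The conclusion assumes two-sided α, equal variances in the two order groups, one averaged value per participant, task and condition, and no differential carryover. The between-participant label is an error regardless of any period effect. Because adjustment is nearly free when no period effect exists, the change is worth making even if drift is expected to be small.

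**What to change.** Average the repeat trials (up to 4 per task and condition) within participant, task and condition. Then replace the paired t test, for bone movement and for skin and liner deformation, with the two-group crossover t test: the mean of the two order groups' mean EV-minus-suction differences, on 19 df. For each task, a linear model with suspension and period as fixed effects and participant as a random effect is equivalent. Averaging matters because a participant-only random effect fitted to single trials would count repeats as independent evidence on EV.

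Describe EV on/off as a within-participant factor in the Overview and Bone Movements sections. If the hierarchical model is used to estimate an EV effect, include suspension and period, and do not adjust that contrast for tibial position measured under each suspension. Do not present results by order group as a test of carryover.

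The cost is 1 degree of freedom and a rewording of the analysis text. No new data are needed, since order is already assigned, and the article places the full analysis after final data collection.

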#### Skin and Liner Deformation

The characterization of 3D skin deformation will be performed by comparing the 3D position of the skin markers at rest, or unloaded position, to the 3D positions of the markers when deformed during each task to produce relative strain assessments for marked regions of the residual limb. The characterization of 3D deformation will be measured between the suspension methods. Paired *t* tests will be performed as previously described for bone movements. Linear regression models will be used to evaluate the potential confounding factors.

#### Power Analysis

Table 1 outlines the sample size estimate required to achieve 90% power for the key variables of interest. A previous pilot investigation for individuals with transfemoral limb loss [23] indicated an effect size of 0.77 for residual femur axial translation. Assuming an α of .05, using paired *t* tests, 21 participants are required to achieve 90% power to detect a 0.5 cm difference in axial translation. Owing to the paucity of highly accurate data on movement between the residual tibia and socket, data from Board et al [1] were used to calculate an effect size for tibia translation (1.75) for suction and EV suspension. Given an effect size of 1.75 and an α of .05 for a paired *t* test, a sample size of 21 will be powered at >99% to detect differences between EV on and off. For skin strain, Gale et al [30] found a maximum shear strain of approximately 0.08. Assuming a shear strain of 0.08 with a moderate effect size of 0.75 (α=.05), a sample size of 21 will be required to achieve 90% power to detect differences between EV on and off.

**Table 1 table1:** Power analysis.

Measure	Values, mean (SD)	Sample size for achieving 90% power, n
Femur distal translation (cm)	2.0 (0.6)	21
Tibial translation (cm)	4.0 (0.4)	6
Skin shear strain	0.08 (0.02)	21

## Results

This study was funded in October 2021. Cadaver testing began in January 2023. Enrollment began in February 2024. Clinical data collection is expected to be completed in December 2025, and the study is expected to be completed in April 2026. Data analysis of the full data set will begin after final data collection. Initial dissemination of results is expected in November 2026, with subsequent publication of secondary analyses in 2027.

## Discussion

### Expected Outcomes and Anticipated Principal Findings

It is expected that the outcomes of this investigation will significantly contribute to the understanding of the complex mechanics of the residual limb-tissue-socket interfaces during dynamic activities for individuals with lower limb loss. It is also expected that by using DSX in combination with novel mathematical algorithms, relative movement between the residual limb and socket and skin deformation can be accurately measured during dynamic motions for individuals with lower limb loss. Ultimately, this foundational information can be critical for developing a database of biomechanical socket parameters deemed important for socket fit, limb health, and comfort. By using the techniques developed in this investigation to perform future comparative effectiveness research of current prosthetic socket technology, better information about the benefits, risks, and costs of different socket options can be generated to provide health care decision makers (eg, patients, clinicians, and policy makers) with highly accurate, evidence-based information. Furthermore, the methodology detailed in this study should speed up the processing time, which, to date, has been burdensome for researchers. This will allow for faster dissemination of information and greater throughput of data to inform clinical guidelines for prosthetic suspension systems. Finally, this investigation can provide vital foundational information that can be used by leading manufacturers in prosthetic design to create enhanced socket technology that has the potential to reduce long-term secondary physical comorbidities and degenerative changes [42].

As the number of individuals with limb loss continues to grow [43], substantial resources will be required for rehabilitation and prosthetic services for this population. Effective outcomes-based clinical practice will be necessary to reduce long-term disabilities associated with prosthetic use. As such, it is the objective of this investigation to examine the dynamic in vivo kinematics between the residual limb and prosthetic socket in 6 DOF of motion, as well as to quantify residual tissue and liner deformation for individuals with transtibial limb loss.

### Dissemination Plan

For large-scale dissemination in the Department of Veterans Affairs and Department of Defense, results will be presented through webinars offered by the Extremity Trauma and Amputation Center of Excellence, which are available across the entire Department of Veterans Affairs and Department of Defense health care networks. These webinars are offered to researchers and health care professionals who provide care for individuals with limb loss. For stakeholders in the civilian health care systems, the outcomes and important techniques developed in this study will be published in highly rated peer-reviewed scientific journals (eg, *Gait & Posture, Clinical Biomechanics, Journal of Biomechanics, Frontiers,* and *Orthotics and Prosthetics International*). The results will also be presented at professional conferences that are specific to clinical limb loss care teams (eg, the American Academy of Orthotists and Prosthetists, American Society of Biomechanics, and Military Health System Research Symposium). The findings and methods of this study will also be directly distributed to industry partners. Because most prosthetic technologies used by veterans and service members with limb loss are developed by industrial entities, sharing new evidence-based information with industry leaders will support the development of future products to better meet the needs of individuals with lower limb loss.

### Limitations

The heterogeneity of the population, including varied ages, etiology of limb loss, prosthesis experience, and time since limb loss, may limit the generalizability of the outcomes to a more diverse population. However, the statistical analysis models will adjust for these specific confounding factors. Although participants will use the same type of prosthetic socket, the ankle-foot devices will not be prescribed, which could introduce additional variability. The tibia and skin markers will likely be manually positioned at every fourth to tenth time frame, which may cause intratracker errors that could be improved with automated algorithms. Finally, the limited field of view for DSX may restrict collecting data for the entire gait cycle and will be unable to record the overall position and orientation of the lower limbs and pelvis that are out of view.

## Appendix

Multimedia Appendix 1 Peer-reviewed summary statement from the Congressionally Directed Medical Research Programs, Orthotics and Prosthetics Outcomes Research Program.

## Abbreviations

CT: computed tomography
DIC: digital image correlation
DOF: degrees of freedom
DRR: digitally reconstructed radiograph
DSX: dynamic stereo x-ray
EV: elevated vacuum
PEQ: Prosthesis Evaluation Questionnaire
VA: Veterans Affairs
